**Table 3 Tab3:** **Definitions of postoperative morbidity and mortality**

Event	Criteria
**Postoperative mortality**	Any reason of death within 90 days after major liver resection.
**Postoperative morbidity**	
Posthepatectomy liver failure	Increasing INR and bilirubin on or after postoperative day 5 plus deviation from regular clinical management (Grade B definition according to the International Study Group of Liver Surgery [ISGLS]) [14].
Cholangitis	Elevation in temperature more than 38.5°C and Leukocytes ≥10*10^9^/L, thought to have a biliary cause, without concomitant evidence of acute cholecystitis, requiring invasive intervention [13].
Hepaticojejunostomy (biliary) leakage	Drainage of fluid with an increased bilirubin level three times greater than the serum level on or after postoperative day three; or the need for interventions as the result of bile collections or biliary peritonitis; or direct visual evidence of defect at anastomoses (definition according to ISGLS) [15].
Intra-abdominal abscess formation	Intra-abdominal fluid collection with positive cultures identified by ultrasonography or computed tomography, associated with persistent fever and elevations of white blood cells [13].
Wound infection	Requiring intervention; otherwise considered as minor complication [13].
Portal vein thrombosis	Conclusive radiologic evidence of thrombosis [13].
Hemorrhage	A drop in haemoglobin level >3 g/dl post-operatively compared with the post-operative baseline level and/or post-operative transfusion of ≥2 units packed red blood cells for a falling haemoglobin and/or the need for radiological intervention (such as embolization) and/or re-laparotomy to stop bleeding (Grade B/C haemorrhage according to ISGLS) [16].
Emergency re-laparotomy	Any (other) reason following major liver resection [13].
Pneumonia	Pulmonary infection with radiological confirmation and requiring antibiotic treatment [13].

### Study outline

The general study outline is presented in Figure 1. All patients with presumed PHC presenting at the participating centers are evaluated in a multidisciplinary team meeting. Patients are eligible for inclusion if all in-and exclusion criteria are met according to the multidisciplinary team meeting based on clinical history and CT and/or MRCP imaging. Next, the type of liver resection indicated is determined in the multidisciplinary team meeting, defining the side of the FLR and primary aim of preoperative biliary drainage. Planned liver resections may consist of right (extended) hemihepatectomy, left extended hemihepatectomy, or left hemihepatectomy: the corresponding FLR that should be drained preoperatively consists of the left liver segments, the right posterior segments, or the right anterior + posterior segments.

**Figure 1 Fig1:**
[figure not shown]
**Flowchart of the study.**

After informed consent has been obtained, patients are randomized to undergo EBD or PTBD of the FLR within 5 days. The allocated drainage procedure should be repeated until internal biliary drainage of the FLR has been achieved (i.e. technical success). Follow-up is done at 7 days after technical success: therapeutic success at follow-up is defined as normal caliber bile ducts in the FLR on ultrasonography and a minimum 20% decrease in the total bilirubin level compared to the reference level at randomization. Additional total bilirubin assessments are performed at 14 days after technical success, and at admission for exploratory laparotomy, to evaluate patency of the biliary drainage. Revisional drainage procedures may be required if complications occur after biliary drainage, as described in Table 2. Complications are treated according to local guidelines. Crossover treatment is allowed if the allocated drainage procedure is considered to be no longer technically feasible (e.g. cholangitis with multiple isolated segments after EBD, requiring additional PTBD).

Additional staging (e.g. percutaneous biopsy or staging laparoscopy) may be used to further determine resectability of the tumor after randomization and initial biliary drainage. Patients who loose eligibility to undergo major liver resection because distant metastases are found at additional staging remain included in the intention-to-treat analysis, as described above.

Exploratory laparotomy is intentionally scheduled at 4 weeks after randomization, or at 6 weeks after randomization if the patient requires portal vein embolization. A radical resection is pursued at exploratory laparotomy if the diagnosis of resectable PHC without distant metastases is confirmed. Resections consist of excision of the liver hilum en bloc with (extended) hemihepatectomy including the caudate lobe, and complete lymphadenectomy of the hepatoduodenal ligament. Portal vein excision and reconstruction are used when necessary. If present, transhepatic percutaneous drains are left in-situ and used as transanastomotic drains to facilitate healing of the hepaticojejunostomies.

### Preoperative biliary drainage

Technical success of biliary drainage is defined as successful stent/catheter placement providing internal biliary drainage of the future liver remnant. Preoperative biliary drainage preferably consists of unilateral drainage of the FLR, but bilateral drainage may be indicated as evaluated by the treating physician (e.g. need for portal vein embolization or bilateral cholangitis) [17].

#### Endoscopic biliary drainage

A sphincterotomy with blended electrosurgical current may be used to facilitate the insertion of multiple stents and/or brush cytology. Opacification upstream of the obstruction is intentionally restricted to segments that are aimed to be drained during the procedure. Bile duct(s) unintentionally opacified upstream from the obstruction should be drained during the same procedure. Polyethylene endoprostheses (size 10Fr) are then pushed in position over the catheter. Directly after the procedure, a 100 mg Diclofenac suppository is administered to the patient for the prevention of post ERCP-pancreatitis [18].

#### Percutaneous transhepatic biliary drainage

The technique of PTBD involves the use of ultrasound guidance, a thin Chiba needle and a 0.014-inch guidewire to gain access to the biliary system. Antegrade cholangiography will be used to localize the site of obstruction. The guidewire is manoeuvred through the stenosis. A catheter is placed with its distal end in the duodenum for internal-external-drainage. Externally draining bile is collected approximately during the first 48 h, after which the catheter is closed in order to achieve internal drainage.

#### Antibiotic treatment

Standard antibiotic prophylaxes are administered at the start of each biliary drainage procedure, according to local protocol as described in an additional file [see Additional file 1]. Prophylactic antibiotic protocols vary between centers, but they are similar for EBD and PTBD procedures in the same center.

### Data collection and monitoring

All preoperative and postoperative complications will be monitored. Patients complete questionnaires (QLQ-C30/BIL21) at the day of randomization, and at 7 days, 28 days, and 90 days after randomization. There will be regular contact between the trial coordinator and the participating centers. Baseline and outcome data are collected by designated data managers using a standardized case record form [see Additional file 2], which is monitored by the trial coordinator.

### Statistical analysis

The DRAINAGE trial is a superiority trial, designed to detect a reduction in the primary outcome measure in favor of PTBD. The analysis will be based on the intention-to-treat principle.

#### Sample size

Determination of the sample size is split in a provisional and definitive calculation, because only little retrospective evidence is currently available for power estimation. A previous study from the primary study center showed a severe complication rate of 60% in the EBD group versus 18% in the PTBD group. In the DRAINAGE trial, a complication rate of 50% is expected after EBD and 25% after PTBD (i.e. a relative decrease of 50%). This estimation was further expanded with proportions for the number of complications, as shown in Table 4. Accounting for a 3% dropout, 53 patients are needed in each arm resulting in a provisional required sample size of 106 patients (Wilcoxon/Mann–Whitney rank-sum test for ordered categories; α = 0.95; β = 0.8).

**Table 4 Tab4:** **The estimated number of complications in each study group used to calculate the provisional sample size**

	EBD	PTBD
0 complications	50%	75%
1 complication	25%	17%
≥2 complications	25%	8%
Total proportion	100%	100%

The estimated proportion of patients is presented for each categorical number of complications.

Interim analysis after inclusion of 53 patients (50%) will provide the definitive sample size, which will be calculated based on the observed number of complications in the EBD group. The definitive sample size will be determined similar to the provisional sample size, again using a relative decrease of 50% in the proportion of complications unless the absolute decrease drops below 20%, which is defined as the lowest absolute decrease with clinical relevance.

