**Methods/Design:**

The study is a multi-center trial with an “all-comers” design, randomizing patients between endoscopic or percutaneous transhepatic biliary drainage. All patients selected to potentially undergo a major liver resection for presumed PHC are eligible for inclusion in the study provided that the biliary system in the future liver remnant is obstructed (even if they underwent previous inadequate endoscopic drainage). Primary outcome measure is the total number of severe preoperative complications between randomization and exploratory laparotomy. The study is designed to detect superiority of percutaneous drainage: a provisional sample size of 106 patients is required to detect a relative decrease of 50% in the number of severe preoperative complications (alpha = 0.95; beta = 0.8). Interim analysis after inclusion of 53 patients (50%) will provide the definitive sample size. Secondary outcome measures encompass the success of biliary drainage, quality of life, and postoperative morbidity and mortality.

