#### Data analysis

The principal analysis consists of an intention-to-treat comparison of the number of preoperative severe drainage-related complications. The research hypothesis will be evaluated using a Wilcoxon/Mann–Whitney rank-sum test with a two-sided 0.05 significance level. The comparison will be expressed in terms of a relative risk and 95% confidence intervals, as determined with multinomial logistic regression.

Subsequent analyses are directed at the secondary endpoints. Continuous data will be presented as the mean with standard deviation or median with interquartile range depending on data distribution, and accordingly evaluated with Mann–Whitney U or t-test statistics. Categorical variables will be evaluated using Pearson’s chi-squared test or Fisher’s Exact test as applicable.

Preplanned subgroup analyses will be based on a dichotomized complication rate to retain statistical power (no complication versus 1 or more complications), and the analyses will consist of logistic regression with the subgroup and randomized treatment added as an interaction term. Subgroup analysis will be performed for patients with Bismuth type 4 tumors, and patients with a left-sided FLR.

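### The definitive sample size is driven by the interim EBD count in about 26 patients with no printed minimum, so a chance-high EBD rate shortens the trial and tilts the final test slightly towards PTBD

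*Protocol article*

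**What the plan says.** The Sample size section plans on the premise that "a complication rate of 50% is expected after EBD and 25% after PTBD", splits these rates into 0, 1 and ≥2 complications in Table 4 (EBD 50/25/25%, PTBD 75/17/8%), and concludes: "Accounting for a 3% dropout, 53 patients are needed in each arm resulting in a provisional required sample size of 106 patients".

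That figure is provisional. The abstract and the Sample size section both state: "Interim analysis after inclusion of 53 patients (50%) will provide the definitive sample size". The section adds that the new number is one "which will be calculated based on the observed number of complications in the EBD group", obtained in the same way as the provisional number, "again using a relative decrease of 50% in the proportion of complications unless the absolute decrease drops below 20" percentage points, the smallest absolute decrease held to be clinically relevant. It prints no minimum, no maximum and no increase-only condition.

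The Data analysis section then compares the arms with a "Wilcoxon/Mann–Whitney rank-sum test with a two-sided 0.05 significance level". It mentions no adjustment for the re-estimation.

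**The concern.** The interim EBD count does two jobs. It is part of the data in the final test, and it alone decides how many more patients are enrolled. If EBD looks bad by chance, the 50% relative decrease becomes a larger absolute target, the required number falls, and the early imbalance keeps more weight in the final data. If EBD looks good by chance, with an observed rate between 50% and 40%, the number rises and the imbalance is diluted. The asymmetry pushes the final test towards PTBD, the arm that the trial is designed to show superior.

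A rate estimated in about 26 patients is also imprecise, so the definitive size may reflect sampling noise more than the true complication rate.

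**Working it through.** **1. The plan's own figure.** The Sample size section prints "rank-sum test for ordered categories; α = 0.95; β = 0.8". I read this as a confidence level of 0.95 (alpha 0.05, two-sided as in Data analysis) and a power of 0.80.

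From Table 4, the probability that an EBD patient fares worse than a PTBD patient, counting ties as one half, is:
- worse: 0.25×0.75 + 0.25×(0.75+0.17) = 0.4175
- ties: 0.5×0.75 + 0.25×0.17 + 0.25×0.08 = 0.4375
- θ = 0.4175 + 0.4375/2 = 0.63625

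The tie-corrected null variance with exact alternative variance gives n = 50.8, so 51 per arm, and 51/0.97 = 52.6, so 53. The plan's figure is reproduced. The simpler tie-corrected Noether formula is n = (1.96+0.8416)² × (1−Σm³) / [6(θ−0.5)²], where m is the mean of the two arms' category proportions. With m = (0.625, 0.21, 0.165), 1−Σm³ = 0.7421 and n = 7.849×0.7421/(6×0.01856) = 52.3. After dropout that is 54 per arm after rounding once (108 in total), close enough to apply the rule.

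**2. The rule by observed EBD rate.** Assumptions: EBD events split evenly between 1 and ≥2; PTBD events in the Table 4 ratio 17:8; 20-point minimum decrease applied; 3% dropout. Example at 60%: EBD 40/30/30 against PTBD 70/20.4/9.6 gives θ = 0.6662, 1−Σm³ = 0.8099 and n = 7.849×0.8099/(6×0.02762) = 38.4. Then 38.4/0.97 = 39.5, so 40 per arm.

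| Observed EBD rate | 30% | 35% | 40% | 45% | 50% | 55% | 60% | 65% | 70% |
|---|---|---|---|---|---|---|---|---|---|
| Total N | 126 | 142 | 154 | 128 | 108 | 94 | 80 | 70 | 60 |

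**3. Precision of the input.** Half of 53 is about 26. At a true rate of 50% the standard error is √(0.25/26) = 0.098, so the observed rate ranges over 50% ± 1.96×9.8 points, or 31 to 69%. That covers almost the whole table.

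**4. Simulation.** Interim counts come from 26 EBD and 27 PTBD patients, N is recalculated by the rule, and the final test is a tie-corrected Wilcoxon at |z| > 1.96, with up to 1,000,000 trials per scenario. There is no floor except patients already enrolled, and a cap of 200 per arm where the rule has no solution.

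No true difference, 50% rate:

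| Rule | False PTBD win | Two-sided |
|---|---|---|
| Fixed 106 | 2.5% | 5.0% |
| As printed | 2.8–3.1% | 5.3–5.5% |
| EBD-based, never below 106 | 2.5–2.6% | 4.9–5.0% |
| Pooled and blinded, never below 106 | 2.5% | 5.0% |

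The 2.8% end comes from halving both severity categories proportionally, the 3.1% end from the Table 4 split. As printed, false EBD wins fall to about 2.3 to 2.4%, and the estimated difference is biased towards PTBD by about 1.2 points under the Table 4 split. Across true rates of 40 to 60%, the PTBD-side error is about 2.85 to 3.0%. At 60%, the loss on the EBD side offsets it (2.85% + 2.16% = 5.0% two-sided).

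The mechanism shows in the trials cut to 80 or fewer, about 17% under the null at a 50% rate. Among these, PTBD is falsely declared better in about 11.7%, against 8.6% when the same interim results are carried on to 106.

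**5. Spread and power at a true EBD rate of 50%.** Before the dropout allowance, N runs from 62 to 152 (5th to 95th percentile), and 44% of trials fall below 102 (2×51, the analysable equivalent of 106). With proportional halving, the range is 82 to 166 and the share is 24%. Under the Table 4 alternative, power is about 86 to 90% with the printed rule and 82% with a fixed 106.

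**The case against.** The strongest reply is that the harm is small. The false-positive excess on the PTBD side is 0.3 to 0.6 points and is partly offset on the other side. Average power is above the planned 80%. The number 106 is labelled provisional because prior evidence was thin, so a smaller trial at a high EBD rate follows from the same relative effect and the same power. All of this stands.

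The article also does not announce a reduction. It is silent, and a minimum may stand in the full protocol, which is not shown. This too stands in part: with a floor the problem almost disappears. But the printed rule recalculates in the same way as before, so taken as written it gives fewer than 106 patients when the observed EBD rate is clearly above 50%. The section itself cites 60% from an earlier study at the primary centre, where the rule gives about 80.

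A third reply is that proportional halving fits the text better and gives milder figures. It is reported above as one end of the range. However, it does not reproduce the plan's number: 50/25/25 against 75/12.5/12.5 gives θ = 0.625 and n = 7.849×0.7427/(6×0.015625) = 62.2 per arm, or about 130 in total after dropout.

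Several stronger inferences are not supported:
- **That announcing N would disclose the EBD rate.** The mapping is not one-to-one (126 at 30%, 128 at 45%), and the article does not say how N is communicated.
- **That the PTBD target could become negative.** This needs at most 5 of 26 EBD patients with events, a chance of about 0.1% at the planned rate.
- **That patients with incomplete follow-up will be counted.** The trigger is worded as inclusion, but nothing says so. Between 50% and 40%, undercounting would enlarge the trial, not shrink it.

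**Conclusion.** The point holds as a modest design flaw. The printed rule links remaining enrolment to the outcome of one arm, and the final test does not allow for it. At a 50% rate the PTBD-side error is about 2.8 to 3.1% instead of 2.5%. The size of the trial varies more than twofold at one and the same true EBD rate.

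A reader might infer that the error rate is seriously broken or that the trial is underpowered. Neither follows: the two-sided error is about 5.3 to 5.5%, and average power is about 86 to 90%.

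The result rests on three assumptions: about 26 EBD patients at the interim, one of the two severity splits, and no minimum elsewhere. If the full protocol already forbids a reduction, only a residue of about 0.1 to 0.2 points at most remains.

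**What to change.** State in the Sample size section that the definitive sample size may not fall below the provisional 106. This alone brings the PTBD-side error to about 2.5 to 2.7% over the rates examined, even with the EBD-only rule. The cost is that no patients are saved when the EBD rate is high.

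Preferably, also re-estimate from the pooled, arm-blinded distribution of complications in the first 53 patients who have completed primary follow-up. Under the assumed 50% decrease with equal arms, the pooled rate is (1 + 0.5)/2 = 3/4 of the EBD rate, so the EBD rate is 4/3 of the pooled rate. Keep the 20-point minimum decrease. With the floor this restores 2.5% per side, with power of about 85% under Table 4.

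The pooled version has two limits. It relies on the assumed relative decrease, and it is nearly as noisy as the EBD-only rule: without the floor, N still ranges from 66 to 156 (95% range). The floor is therefore the essential part. Both changes are wording only.

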#### Data analysis

The principal analysis consists of an intention-to-treat comparison of the number of preoperative severe drainage-related complications. The research hypothesis will be evaluated using a Wilcoxon/Mann–Whitney rank-sum test with a two-sided 0.05 significance level. The comparison will be expressed in terms of a relative risk and 95% confidence intervals, as determined with multinomial logistic regression.

Subsequent analyses are directed at the secondary endpoints. Continuous data will be presented as the mean with standard deviation or median with interquartile range depending on data distribution, and accordingly evaluated with Mann–Whitney U or t-test statistics. Categorical variables will be evaluated using Pearson’s chi-squared test or Fisher’s Exact test as applicable.

Preplanned subgroup analyses will be based on a dichotomized complication rate to retain statistical power (no complication versus 1 or more complications), and the analyses will consist of logistic regression with the subgroup and randomized treatment added as an interaction term. Subgroup analysis will be performed for patients with Bismuth type 4 tumors, and patients with a left-sided FLR.

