### Design

The present study is a multicenter randomized controlled superiority trial. Patients are randomized to preoperative EBD or PTBD by minimization using computer-generated allocation (www.tenalea.net). The randomization procedure is stratified for three factors, including: (attempted) biliary drainage procedures before referral to the enrolling center (drainage naïve versus drainage non-naive); the level of bile duct involvement (Bismuth type 1, 2, 3A or 3B versus type 4); and enrolling center.

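### Allocation is minimized on three factors that the principal rank-sum test ignores; to the extent they predict complications, the test is conservative and some power is forgone

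*Protocol article*

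**What the plan says.** On allocation, the Design section states: "Patients are randomized to preoperative EBD or PTBD by minimization using computer-generated allocation". The factors are earlier (attempted) drainage before referral, then "the level of bile duct involvement (Bismuth type 1, 2, 3A or 3B versus type 4); and enrolling center".

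On analysis, the Data analysis section makes the intention-to-treat comparison of the number of severe complications the principal analysis. It tests this with a "rank-sum test with a two-sided 0.05 significance level" and adds: "The comparison will be expressed in terms of a relative risk and 95% confidence intervals, as determined with multinomial logistic regression". No stratification or covariate is named for the test or the model. Bismuth type 4 returns only as a subgroup interaction on a dichotomized outcome. Drainage history and center appear in no stated analysis.

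The Sample size section sizes the trial for the same plain rank-sum test, using the three ordered categories of Table 4.

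**The concern.** The rank-sum variance is derived as if any split of the patients between arms were equally likely. Minimization rules out splits that are unbalanced on the three factors. If the factors predict the outcome, the test statistic varies less than the test assumes, because the between-patient variation due to the factors can no longer fall unevenly between arms. The plain test still counts that variation as error.

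If the factors explain a share R² of the variance of the ranks and balance is close, the true null variance is roughly (1 − R²) times the assumed one. The actual two-sided error is then about 2 × [1 − Φ(1.96/√(1 − R²))], which is below 0.05 whenever R² > 0. An analysis that includes the factors removes the same share from the error term and gains power.

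What is at stake is efficiency. The Discussion says that the rarity of the disease makes accrual hard and that all specialist centers in the country are already taking part. Power obtainable without recruiting another patient is therefore worth having.

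**Working it through.** **1. Reproducing the planned size.** Inputs from Table 4: EBD 50/25/25% and PTBD 75/17/8% for 0, 1 and ≥2 complications; dropout 3%. The printed "rank-sum test for ordered categories; α = 0.95; β = 0.8" is read as two-sided α 0.05 and power 0.80.

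- Probability that an EBD patient has more complications, ties counted half: θ = 0.25 × 0.75 + 0.25 × (0.75 + 0.17) + 0.5 × (0.50 × 0.75 + 0.25 × 0.17 + 0.25 × 0.08) = 0.4175 + 0.21875 = 0.63625.
- Tie-corrected null variance term V0 = 0.12368; variance term under the alternative V1 = 0.11242.
- n per arm = (1.96 × √0.12368 + 0.8416 × √0.11242)² / (0.63625 − 0.5)² = (0.6893 + 0.2822)² / 0.018564 = 50.8, so 51.
- 51/0.97 = 52.6, so 53 per arm and 106 in total, as stated. A one-sided test gives 39.9 before dropout and does not fit.
- Direct simulation of the plain test at 51 per arm under simple randomization: power 0.805, type I error 0.050.

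**2. Effect of minimization.** Simulation with 102 patients and 20,000 trials per scenario. Table 4 marginal rates are held fixed in each arm. Minimization is on the three factors, with a biased coin of 0.8 or fully deterministic. *Assumptions, because the documents are silent:* 30% drainage naive, 40% Bismuth 4, four centers, and the same odds ratio (OR) for each factor. The adjusted test is a rank analysis of covariance on the three factors.

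| OR per factor | Type I error, unadjusted (coin 0.8 / deterministic) | Power, unadjusted (coin 0.8) | Power, adjusted (coin 0.8) | Gain, points |
|---|---|---|---|---|
| 1 | 0.051 / 0.050 | 0.803 | 0.801 | −0.2 |
| 1.5 | 0.048 / 0.049 | 0.808 | 0.814 | +0.6 |
| 2 | 0.040 / 0.043 | 0.811 | 0.828 | +1.7 |
| 3 | 0.034 / 0.030 | 0.824 | 0.865 | +4.1 |
| 4 | 0.023 / 0.023 | 0.823 | 0.887 | +6.4 |

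Type I error of the adjusted test lay between 0.048 and 0.053 throughout. The Monte Carlo standard error near 5% is √(0.05 × 0.95/20,000) = 0.0015, so the departures at OR 2 and above are not simulation noise.

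**3. Link to the formula.** Inverting the approximation above, an error of 0.040 corresponds to z = 2.054 and R² = 1 − (1.96/2.054)² ≈ 0.09. An error of 0.034 corresponds to z = 2.120 and R² ≈ 0.15. The effect is material only if the factors explain roughly a tenth or more of the rank variance.

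**4. Second simulation.** Same size and fixed Table 4 rates, with unequal ORs for drainage history and Bismuth type. At 1.5/1.5, 2/1.5 and 3/2, type I error of the unadjusted test was 4.4%, 4.1% and 3.5%, against 4.4-5.0% adjusted. Power gains were about 0.5, 1.3 and 2.4 points.

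**The case against.** **A reader might infer that the trial is underpowered.** The documents do not support this. With Table 4 rates held fixed, unadjusted power is 0.80 to 0.82 in every scenario. It rises slightly with prognostic strength, because balance makes the statistic less variable around a mean that already lies beyond the critical value. A simulation can show power of 75.8% or 69% by applying the log odds ratio of 1.14 fitted from Table 4 as an effect within factor levels. Table 4 gives marginal rates, and that step shrinks the marginal effect. With ORs of 4 and 3 the PTBD complication rate becomes about 28% instead of 25%, and power is about 67% at 53 per arm even under simple randomization. The shortfall reflects mainly a smaller assumed effect, not the mismatch between allocation and test.

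**A reader might infer a failure of error control.** It is not one. The 0.05 level is respected as an upper bound, and a positive result would stand.

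**The size is not known.** This objection holds. The article hints that the factors matter: proximal tumors are hard to cannulate and undrained segments can lead to cholangitis, complications are managed by local guidelines, and antibiotic protocols differ by center. It gives no odds ratios. Requiring recovery from earlier drainage and at least 5 days off antibiotics may also weaken drainage history as a predictor.

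**An article condenses the full protocol.** This holds in part. The primary test and its level are fixed in the article, so that choice can be questioned. Which covariates enter the multinomial model is simply not stated, and that silence is not counted as an error.

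**The remedy is not free.** A proportional-odds model adds an assumption. Table 4 itself implies ORs of (0.50/0.50)/(0.25/0.75) = 3.0 for ≥1 complication and (0.25/0.75)/(0.08/0.92) = 3.83 for ≥2, a modest departure. The tabulated gains are for the covariate-adjusted rank test; other adjusted methods should behave similarly but not identically.

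**Conclusion.** The point holds as one of efficiency. The allocation uses three factors that the principal test ignores, so the test is conservative and less powerful than an adjusted one to the extent that those factors predict complications. At assumed ORs of 1.5-2 the effect is small; at 3-4 it is worthwhile, at about 2-6 points of power. With no prognostic effect nothing is gained and about 0.2 points is lost. These ranges rest on assumed prognostic strengths, factor prevalences and number of centers, none of which the documents give. The planned sample size is right for the stated test and needs no correction on this account. The change is advisable but not essential to the trial's validity.

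**What to change.** Make the principal test one that is adjusted for the minimization factors. Suitable choices are:

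- a covariate-adjusted rank test, or a proportional-odds model of the ordered count (0, 1, ≥2), with treatment, drainage history, Bismuth 4 versus other, and center (small centers pooled or as a random effect); or
- a van Elteren test stratified by drainage history × Bismuth type, which avoids the proportional-odds assumption but omits center and so gains slightly less.

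Put the same factors in the model that yields the effect estimate and its interval, and keep the unadjusted rank-sum test as a supportive analysis. Specify the pooling rule for centers and the exact model before outcomes by arm are seen, preferably before the interim look at 53 patients, which uses complication counts from the EBD arm.

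The cost is a change of analysis wording. All three factors are recorded at randomization, so no new data are needed and the sample size can stay. The drawbacks are the handling of sparse centers and, for the proportional-odds option, one more model assumption.

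### The primary effect is promised as a single relative risk from multinomial logistic regression, but that model's coefficients are category-wise odds ratios and no contrast is named

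*Protocol article*

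**What the plan says.** In the protocol article, Data analysis, the primary hypothesis is to be "evaluated using a Wilcoxon/Mann–Whitney rank-sum test with a two-sided 0.05 significance level". The next sentence fixes how the result is reported: "The comparison will be expressed in terms of a relative risk and 95% confidence intervals, as determined with multinomial logistic regression". It speaks of one relative risk. It does not say which category or contrast that figure refers to, or how it is obtained from the model.

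The Sample size section sets the yardstick. It expects complications in 50% of patients after EBD and 25% after PTBD, a halving. When the definitive sample size is set, the halving is kept unless the absolute decrease falls below 20 points, the smallest decrease regarded as clinically relevant. Table 4 divides the rates into 0, 1 and ≥2 complications: 50/25/25% for EBD and 75/17/8% for PTBD. The calculation uses a "Wilcoxon/Mann–Whitney rank-sum test for ordered categories; α = 0.95; β = 0.8".

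**The concern.** A multinomial logistic model compares each non-reference category with the reference category. Its exponentiated treatment coefficient for category k is the ratio between arms of P(k)/P(0). This is a baseline-category odds ratio; some software prints it as a relative risk ratio, which invites confusion with a relative risk. With three categories there are two such ratios, and the model makes no use of their order, although the test and the sample size both rest on ordered categories.

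Three things are at stake:

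- **Labelling.** Complications are expected in a quarter to a half of patients, so odds-type ratios lie well away from risk ratios. Reporting one as the other would exaggerate the effect.
- **Choice of headline.** With two ratios and neither named in advance, the single reported figure could be chosen after the results are known.
- **Interpretation.** The planned effect and the relevance threshold concern the proportion of patients with complications. The coefficients cannot be set against either.

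**Working it through.** **Inputs** (Sample size section and Table 4)

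| Complications | EBD | PTBD |
|---|---|---|
| 0 | 0.50 | 0.75 |
| 1 | 0.25 | 0.17 |
| ≥2 | 0.25 | 0.08 |

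The significance level is two-sided 0.05 (Data analysis). The printed α = 0.95 and β = 0.8 are read as confidence 0.95 and power 0.80. Dropout is 3%, with 53 patients per arm.

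**Step 1: reproduce the plan's sample size.**

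- P(PTBD patient has fewer) = 0.25×0.75 + 0.25×0.75 + 0.25×0.17 = 0.4175.
- P(tie) = 0.50×0.75 + 0.25×0.17 + 0.25×0.08 = 0.4375.
- Mann–Whitney probability = 0.4175 + 0.4375/2 = 0.636.
- Simulation of the tie-corrected test (40,000 trials per size) gives power 0.795 with 50 per arm and 0.804 with 51. Then 51/0.97 = 52.6, so 53 per arm and 106 in total, as stated.
- The tie-corrected formula gives 52.3 per arm before dropout and 53.9 after, so 54. This is within one patient per arm.

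The planned test and N are therefore sound on their own terms.

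**Step 2: what the coefficients would be if Table 4 were exactly true.** The formula is exp(b_k) = [P_k/P_0 in PTBD] / [P_k/P_0 in EBD].

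- 1 vs 0: (0.17/0.75)/(0.25/0.50) = 0.453.
- ≥2 vs 0: (0.08/0.75)/(0.25/0.50) = 0.213.

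Fitting a multinomial model to the Table 4 proportions returns the same two values.

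**Step 3: the risk ratios.**

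| Contrast | Risk ratio | Risk reduction | Multinomial ratio | Reduction if misread |
|---|---|---|---|---|
| Exactly 1 | 0.17/0.25 = 0.68 | 32% | 0.453 | 55% |
| ≥2 | 0.08/0.25 = 0.32 | 68% | 0.213 | 79% |
| Any (≥1) | 0.25/0.50 = 0.50 | 50% | none | none |

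The absolute decrease for any complication is 50 − 25 = 25 points.

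**Step 4: direction of the distortion.** Each multinomial ratio equals the category risk ratio divided by the risk ratio for having no complication. Here the divisor is 0.75/0.50 = 1.5, so 0.68/1.5 = 0.453 and 0.32/1.5 = 0.213. With the arms exchanged, the risk ratios become 1/0.68 = 1.47 and 1/0.32 = 3.13, and the multinomial ratios 1/0.453 = 2.21 and 1/0.213 = 4.69. The exaggeration follows the observed effect and disappears when the arms do not differ. This assumes that both complication categories move the same way, as in Table 4.

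**Step 5: the same model's fitted probabilities.** With treatment as the only covariate, the fitted probabilities reproduce the proportions in each arm. Risk ratios taken from them are 0.68, 0.32 and 0.50, exactly as in Step 3.

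**Step 6: agreement with the test at 53 per arm under Table 4.** The standard error of the log ratio is √(sum of 1/expected cell count over the four cells).

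- 1 vs 0: approximate 95% CI 0.17 to 1.21.
- ≥2 vs 0: approximate 95% CI 0.06 to 0.71.

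In 40,000 simulated trials the rank-sum test was significant in 82%. Among those, the 1 vs 0 ratio was significant in 42% and the ≥2 vs 0 ratio in 89%. The message can therefore depend on which ratio is shown.

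**The case against.** A reader might infer that the reported figure is bound to overstate the benefit. The article does not support that. It promises a relative risk and never says that the coefficients will be reported as one. Step 5 shows that the named model can deliver correct risk ratios. The overstatement depends on a reporting step that the text neither states nor excludes.

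Other stronger readings also fail:

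- **Bias towards PTBD.** Step 4 shows that misread coefficients would exaggerate harm from PTBD just as they would exaggerate benefit.
- **The model cannot give the design quantities and must be dropped.** Its fitted probabilities give both the any-complication risk ratio of 0.50 and the 25-point difference. Only the coefficients fail to.
- **The model creates the instability in the ≥2 category.** About 4 PTBD patients (8% of 53) are expected there whatever the method. The log-scale standard error is about 0.61 for the multinomial ratio and about 0.52 for a direct risk ratio, a modest gap.
- **A mismatch with the rank-sum test condemns the plan.** A rank test with a separate descriptive effect measure is common. Even a plain risk ratio for any complication disagreed with the rank-sum test on significance in about 8% of simulated trials.

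It can also be said that the exact contrast belongs in a fuller protocol or analysis plan, which is not at hand. That has weight for the contrast alone. But the article itself fixes both the measure and the model, and as written they do not fit each other.

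**Conclusion.** The point holds as a mismatch between a stated measure and a stated model, with no contrast named. On the trial's own Table 4, the coefficients would be 0.45 and 0.21, against category risk ratios of 0.68 and 0.32 and a planned any-complication risk ratio of 0.50. The exaggeration arises only if the coefficients are labelled relative risks; the lack of a defined contrast remains on either reading.

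The rank-sum test, its p-value, the superiority decision and the sample size are untouched. This should be fixed, but it does not threaten the trial's main inference.

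The figures assume that Table 4 holds, that the model uses the same three categories (the article states them only for the sample size; more categories would mean more ratios), and that treatment is the only covariate.

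**What to change.** Replace the sentence on the relative risk with wording along these lines:

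> The effect of PTBD versus EBD will be reported as the risk ratio and the risk difference, each with a 95% confidence interval, for having at least one severe drainage-related complication. The rank-sum test will be accompanied by the Mann–Whitney probability (the chance that a PTBD patient has fewer complications than an EBD patient, counting ties as one half) with its 95% confidence interval.

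Name one method for the risk ratio: log-binomial regression, or modified Poisson regression with robust standard errors. The risk difference can come from the corresponding identity-link model or from fitted probabilities. If the multinomial model is kept, state that both measures are computed from its fitted probabilities and that its coefficients will not be reported as relative risks. A proportional-odds ratio could replace the Mann–Whitney probability, but one ordinal measure should be chosen in advance.

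The reported effect can then be read directly against the 50% relative and 20-point absolute decreases. Under Table 4 it would be a risk ratio of 0.50, a difference of 25 points and a Mann–Whitney probability of 0.636. The change needs no new data or patients and leaves N as it is. It should be made before outcomes are compared by arm.
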